## Abstract

**Background and Aims:**

The growing burden of chronic diseases highlights the need for valid instruments to assess quality of life in palliative care. The Functional Assessment of Chronic Illness Therapy‐Palliative (FACIT‐Pal) measures quality of life in patients with chronic illness receiving palliative care. Although it has been validated in 22 other languages, a Persian version has not yet been translated. This study aims to cross‐culturally adapt and evaluate the psychometric properties of the Persian version of the FACIT‐Pal for Iranian patients.

**Methods:**

This cross‐sectional methodological study is designed to cross‐culturally adapt and evaluate the psychometric properties of the FACIT‐Pal in Iranian individuals with cancer and heart failure. Following FACIT translation guidelines, the process will include two forward translations, reconciliation, backward translation, final review, and qualitative cognitive interviews with 10 patients. Feedback from these patients will be analyzed to further refine the translation. After finalizing the Persian version, 552 Iranian inpatients and outpatients with cancer and heart failure at Imam Khomeini Hospital Complex will be invited to participate after providing written informed consent. Inclusion criteria will be: consent; diagnosis with heart failure or cancer; 18 years of age or older; literacy in Persian. Exclusion criteria will be: diagnosed and documented untreated psychological disorders in their medical record that significantly impair their functioning and ability; having uncorrected communication issues; and completion of less than 80 percent of the meassure. Cronbach's alpha and composite reliability will be used to assess reliability. Construct validity will be examined using confirmatory factor analysis. Statistical tests will be performed using SmartPLS and R software.

**Conclusion:**

The Persian version of the FACIT‐Pal questionnaire is expected to have good psychometric properties, including satisfactory validity and reliability. This instrument could be used as a standard scale to measure the quality of life of patients receiving palliative care in Iran.

**Trial Registration:**

Not applicable.

**Clinical Trial Number:**

Not applicable.

AbbreviationsAGFIAdjusted Goodness of Fit IndexAHAAmerican Heart AssociationCFAConfirmatory Factor AnalysisCFIComparative Fit IndexCOSMINCOnsensus‐based Standards for the Selection of Health Measurement INstrumentsEORTC QLQ‐C15‐PALEuropean Organization for Research and Treatment of Cancer Quality of Life Questionnaire – Palliative CareFACIT‐PalFunctional Assessment of Chronic Illness Therapy – Palliative CareFACIT‐Pal‐14Short Form of the Functional Assessment of Chronic Illness Therapy – Palliative Care 14 ‐item versionFACIT‐SpFunctional Assessment of Chronic Illness Therapy – Spiritual Well‐beingFACT‐GFunctional Assessment of Cancer Therapy – GeneralFACT‐G7Functional Assessment of Cancer Therapy – General 7‐item versionGFIGoodness of Fit IndexIKHCImam Khomeini Hospital ComplexMLHF‐QMinnesota Living with Heart Failure QuestionnairePHCPrimary Health CareRMSEARoot Mean Square Error of ApproximationSPSSStatistical Package for the Social SciencesSRMRStandardized Root Mean Square ResidualSTROBEStrengthening the Reporting of Observational Studies in EpidemiologyTLITucker–Lewis IndexTUMSTehran University of Medical SciencesWHOWorld Health Organization

## Background

1

Chronic diseases are conditions that may last for at least for 3 months and may worsen over time [1]. The prevalence of chronic diseases has been increasing, making them the major cause of morbidity and resulting in 75% of global mortality in the world each year [2, 3]. Also, a significant portion of annual health expenditure in the USA is attributed to the chronic diseases [4]. In Iran, the aged population is increasing in parallel with the chronic diseases prevalence, such as ischemic heart diseases, stroke, and diabetes, resulting in an estimated 82 percent of mortality [5, 6]. Also, chronic diseases impose a huge burden on the Iranian healthcare workforce [7].

Among chronic conditions, the incidence of cancer is rapidly increasing. According to the American Cancer Society, about 20 million people were diagnosed with cancer in 2022, and this number is anticipated to increase to 35 million by 2050 [8, 9]. Cancer may influence patients’ lives in various aspects and interfere with their quality of life, which makes it a large concern. In a meta‐analysis, it is estimated that quality of life is significantly affected from 2 to 26 years after cancer diagnosis [10]. Therefore, measuring the quality of life among patients suffering from cancer is a key factor in controlling, managing, and treating the disease [11].

In addition to cancer, heart failure is a quite prevalent chronic condition in Iran, and results in debilitating conditions among patients [12]. It is shown that patients with heart failure experience significantly reduced quality of life in Iran [13]. This condition may originate from various complications (like liver and kidney diseases, arrhythmias, or readmissions) or comorbidities, which could severely decrease their quality of life [14, 15].

According to the World Health Organization (WHO), “quality of life is a concept which aims to capture the well‐being, whether of a population or individual, regarding both positive and negative elements within the entirety of their existence at a specific point in time” [16]. Due to the traumatic influence of chronic diseases, measuring quality of life is considered critical in patients with cancer and heart failure [17].

Palliative care, as an approach aimed to alleviate pain and suffering among patients with chronic diseases, can be applied to patients and their families. Ultimately, it seeks to optimize the quality of life for patients and their families [18]. While much research has focused on palliative care for patients with cancer, patients with heart failure also require high‐quality palliative care due to the significant burden of their disease [19]. In the Primary Health Care (PHC) system in Iran, palliative care is not highlighted adequately and is counted as a novel approach to terminally and/or chronically ill patients [20, 21]. The WHO introduces palliative care as an effective strategy to enhance quality of life among individuals with cancer and their families, as it can ease about 90 percent of physical, psychological, and spiritual distress [9]. On the other hand, the American Heart Association (AHA) has pinpointed applying palliative care besides usual care [22]. Bagheri et al. suggest future research focus on core elements of palliative care, such as quality of life [23].

As mentioned above, a primary goal in palliative care is to optimize patients’ quality of life. Thus, in order to measure the effectiveness of palliative interventions, the presence of an accurate, valid, and reliable scale is crucial. Over the past decades, the assessment of quality of life has gained significance to ensure that clinical and care‐related decisions align with patients’ perspectives [24]. In a systematic review, the absence of a comprehensive quality‐of‐life measurement for Iranian patients with cancer has already been reported [25]. One of the most recent questionnaires validated in Iran is the “Minnesota Living with Heart Failure Questionnaire (MLHF‐Q)”. This questionnaire is specifically produced to evaluate the quality of life among the individuals suffering from heart failure. This questionnaire measures patients’ physical, mental, and social conditions using 21 items [26]. However, it is specific to individuals with heart failure and generalizing it to other chronic conditions needs more investigations. Moreover, the FACIT‐Pal (in comparison with the MLHF‐Q) evaluates the quality of life of general chronic illness in palliative care patients. It focuses on Physical well‐being, Social well‐being, Emotional well‐being, and Functional well‐being, and palliative‐specific items [27].

King et al. compared four Quality of life scales: EORTC QLQ‐C15‐PAL, FACT‐G7, FACIT‐Pal and short‐form FACIT‐Pal‐14 in palliative care settings. Among these, FACIT‐Pal had a better internal consistency. Also, FACIT scales had better test–retest reliability [28]. The FACIT scale is considered a reliable and valid measurement worldwide [29]. This scale was developed by Cella and colleagues [30], and managed by the internationally known FACIT organization [31], creating more than 100 scales, some of which have been translated and linguistically validated into over 80 languages [32].

The 27‐item FACT‐G core module, published in 1993, was initially developed for patients with cancer before broadening to include other chronic illnesses [29, 30]. One such broadened instrument included the 19‐item palliative care specific module, which was added to the FACT‐G, resulting in the 46‐item FACIT‐Pal. Items from the questionnaire were based on interviews of patients and their families [27]. Greisinger et al., [33] have interviewed 194 patients suffering from life‐limiting illnesses and measured their concerns in terms of different aspects of quality of life. The palliative care subscale contains items related to signs and symptoms patients experience in the advanced phase of their illness [27, 33]. The FACIT Pal was subsequently tested by Lyons and colleagues (2009) for reliability and validity [27, 29]. One of the advantages of the FACIT‐Pal scale is its dedication to palliative care, ease of administration, and focus on social well‐being in comparison to other, similar measurements. Also, the scale has shown satisfactory reliability and validity in 22 different languages [34, 35]. It has been translated and psychometrically assessed in regions such as Turkey [36], Spain [37], Germany [38], South Africa, Kenya, and Uganda [29], and recently in China [39].

Cultural adaptation is a crucial part of developing correct and effective principles for implementing care programs in different communities [40]. Despite having satisfactory reliability and validity in multiple languages, the FACIT‐Pal scale has not yet been translated into Persian and assessed in Iranian culture. Given the special linguistic and cultural characteristics of the Persian‐speaking population, strict cultural adaptation and psychometric testing of the FACIT‐Pal scale are absolutely necessary for its accurate implementation in the Iranian palliative care context. Thus, this study primarily aims to cross‐culturally adapt the FACIT‐Pal scale into Persian using a forward‐backward translation method and cognitive interviews (in accordance with the FACIT guidelines), and ensure its equivalence with its original English version, and assess its psychometric properties.

## Methods

2

### Study Design and Setting

2.1

This methodological study will be done cross‐sectionally at the Imam Khomeini Hospital Complex (IKHC) affiliated with the Tehran University of Medical Sciences (TUMS). IKHC is the largest tertiary referral hospital in Iran, comprising Vali‐e‐Asr Hospital, Imam Khomeini Hospital, and the Cancer Institute. Together, they have nearly 400 faculty members, about 4000 administrative and clinical staff, and more than 1000 active beds [41]. Inpatients or outpatients diagnosed with heart failure or cancer, who meet the inclusion and exclusion criteria, will be invited to participate. The protocol of this study is approved by the Research Ethics Committees of TUMS (IR. TUMS. MEDICINE. REC.1403.432) and patients will be asked to provide written informed consent. This study aims to assess the psychometric properties of the Persian version of the FACIT‐Pal scale and will be carried out in two main phases. This protocol adheres to the STROBE (Strengthening the Reporting of Observational studies in Epidemiology) and COSMIN guidelines [42, 43]. The study process is briefly illustrated in Figure 1.

**Figure 1 hsr272068-fig-0001:**
[figure not shown]
The brief illustration of the study process.

### Phase 1: Cross‐Cultural Adaptation and Harmonization

2.2

The copyright of the FACIT questionnaires entirely belongs to the FACIT organization. This study will be conducted after obtaining the written permission letter from the FACIT organization, using the standardized multilingual and validation measurement system [44, 45]. This ensures that the translation of the FACIT‐Pal questionnaire into Persian contains the sufficient quantitative criteria equivalent to the original version of FACIT‐Pal [46]. The written permission was obtained from FACIT.org on September 2, 2024.

The translation phase consists of two forward translations, one reconciliation of the two forward translations, and one backward translation. Initially, two bilingual Iranians—literate in English—will translate the English version to Persian (Forward translation). Afterward, another Persian‐speaking person makes a unified version of the Persian version out of the two forward translations. This unified version is then translated into English by an English‐speaking bilingual who is literate in Persian. If no translation issues are identified, an expert in the field of medical sciences will review the final version of the Persian translation and, if there are any content problems, will express his/her opinions to the team leader.

Once the Persian translation is finalized, cognitive structured interviews will be conducted based on the organization's standard guidelines. This will involve one experienced researcher who is familiar with the questionnaire, palliative care, and qualitative studies, and who has cognitive interview experience. Ten Persian‐speaking patients will complete the FACIT measure and their feedback will be analyzed to further refine the translation, if necessary. After the final application of the patients’ comments, the process of translation and harmonization of the questionnaire will be completed. It is noteworthy that all these steps will be supervised by [name], the Translations Manager of the FACIT organization, and the principal investigator of the research team, [name], will remain in contact with him throughout the translation process.

### Phase 2: Data Gathering & Psychometric Assessment

2.3

#### Data Gathering

2.3.1

##### Participants

2.3.1.1

The study sample will be divided into two groups: (1) Patients with heart failure, comprising 50 percent (276 patients) of the total sample size, will be recruited from CCU, cardiology wards, and the heart failure clinic of IKHC; and (2) Patients with cancer: comprising 50 percent (276 patients) of the total sample size, will be recruited from the cancer institute (oncology ward) of IKHC and the cancer clinics of IKHC. The inclusion criteria will be: (1) consent to participate in the study; (2) diagnosed with heart failure or cancer; (3) 18 years of age or older; (4) having the literacy to read and write in Persian. The exclusion criteria will be: (1) presence of a documented, untreated severe psychological disorder recorded in the medical record by a psychiatrist or treating physician, including schizophrenia spectrum disorders, bipolar disorder, or active substance use disorder, which is considered to cause significant functional impairment, defined as impaired judgment, cognition, or communication that interferes with the individual's capacity to understand study procedures or complete study assessments; (2) uncorrected communication impairments (auditory, visual, or verbal) that preclude participation; and (3) completion of less than 80% of the study measures.

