### Sampling Process

2.5

Among the individuals with cancer and heart failure referred to the inpatient wards and heart failure and cancer outpatient clinics of the IKHC, 552 patients will be selected as the research sample by the convenience sampling method, based on inclusion and exclusion criteria. Of the desired sample size, 50% will be allocated to patients with heart failure (276 patients) and 50% to patients with cancer (276 patients). The necessary matters regarding the study process, the objectives of the research, as well as the confidentiality of their information, will be explained to the patients, and they will be invited to participate in the present study if they wish. Written informed consent will be obtained, and the research instruments, including the demographic questionnaire and the FACIT‐Pal questionnaire, translated into Persian, will be provided. Patients will be asked to complete the questionnaire using a self‐report approach.

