In the Iranian context, there are alternative FACIT scales with different subscales. Out of these, the Persian version of FACIT‐Sp has been validated in 2013 by Jafari et al. the goal of their study was to translate and investigate the reliability and validity of the Persian version of the FACIT‐Sp among Muslim Iranians in treatment for cancer. The Cronbach's alpha coefficient in the Persian version of FACIT‐Sp ranged from 0.72 to 0.90, which showed sufficient reliability [52]. Similar to this study, our research will be conducted among Iranian patients who are predominantly Muslim. However, the focus of this study was limited to patients diagnosed with cancer.

The concept of palliative care is not sufficiently understood by the public and also health‐care staff, which has led to a lack of knowledge about its beneficial outcomes [50]. A reliable and valid tool for measuring quality of life is essential for evaluating the quality of services, the effectiveness of care and treatments, and the impact of interventions [53]. Also, it is mentioned that the community and cultural context could significantly impact the feasibility of the interventions that are implemented, and this shows how culture could be tremendously effective [40]. Moreover, the lack of a gold standard questionnaire, along with a variety of quality‐of‐life scales, has made it difficult to make a comprehensive evaluation of quality‐of‐life [53]. The FACIT‐Pal instrument has yet to be translated into Persian and assessed psychometrically in Iranian culture. Thus, this study could be an outstanding step approaching the optimum quality‐of‐life in Iranian people receiving palliative care.

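### The sample is not restricted to patients receiving palliative care, yet the conclusion is about them, and no reliability or factor analysis by palliative status or stage is stated

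*Protocol article*

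**What the plan says.** **Who is enrolled.** Section 2.3.1.1 (Participants) asks for consent, literacy in Persian, and a patient "diagnosed with heart failure or cancer; (3) 18 years of age or older". The Methods paragraph of the abstract gives the same criteria. Heart failure patients "will be recruited from CCU, cardiology wards, and the heart failure clinic of IKHC"; cancer patients "will be recruited from the cancer institute (oncology ward) of IKHC and the cancer clinics of IKHC". No palliative service is named as a source. Section 2.5 (Sampling Process) adds that "552 patients will be selected as the research sample by the convenience sampling method".

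**Whom the instrument and the conclusion address.** The abstract says that the FACIT-Pal "measures quality of life in patients with chronic illness receiving palliative care". The Background says that the palliative subscale covers "signs and symptoms patients experience in the advanced phase of their illness", and section 2.4 traces its 19 items to interviews with advanced-cancer patients. The abstract concludes: "This instrument could be used as a standard scale to measure the quality of life of patients receiving palliative care in Iran". The Discussion likewise describes the study as a step towards optimum quality of life "in Iranian people receiving palliative care".

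**What is recorded and analysed.** Section 2.4 gives examples of clinical variables: disease type, heart failure classification, cancer type, metastasis, inpatient or outpatient referral, length of stay and comorbidities. Section 2.6.1 reports reliability overall and in the two disease groups, and tests measurement invariance between those groups. Disease stage enters only the known-groups ANOVA. Section 3.1 (Limitations) discusses the single tertiary centre but not palliative status.

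**The concern.** Alpha, omega and CFA fit describe a scale in a particular population. They change with the spread of true scores and with how many patients sit at the end of the response range. An adult with recently diagnosed early cancer or mild heart failure qualifies here, while the palliative items were written around advanced illness. If the study runs as written, its coefficients will describe a convenience mix of hospital patients with cancer or heart failure. The abstract would then carry them over to patients receiving palliative care, a group that the described data do not identify.

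What is at stake is whether the closing claim has support. Later users may choose the Persian scale for palliative-care studies on the strength of coefficients that were never reported for such patients.

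**Working it through.** **1. Populations side by side.**

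| Element | Population |
|---|---|
| Instrument's purpose (abstract) | chronically ill patients receiving palliative care |
| Source of the 19 palliative items (2.4) | patients with advanced cancer |
| Eligibility (2.3.1.1) | any adult with cancer or heart failure who consents and is literate in Persian |
| Recruitment (2.3.1.1, 2.5) | CCU, cardiology and oncology wards, heart failure and cancer clinics; convenience sample |
| Reliability and invariance (2.6.1) | reliability overall and by cancer versus heart failure; invariance between these two groups |
| Conclusion (abstract) | patients receiving palliative care in Iran |

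The Background also says that palliative care receives too little emphasis in Iran's primary health care system and counts as a novel approach there. An unselected hospital sample therefore cannot be presumed to consist of palliative-care recipients.

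**2. The plan's sample size.** Section 2.6 uses 10 patients for each of 46 items: 46 × 10 = 460. Adding 20% gives 460 × 1.20 = 552, which reproduces the stated figure. The next step uses the 460 that the plan wants to analyse.

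**3. How many palliative-care recipients that might contain.** The documents do not give the share *s*, so it is an assumption. Recipients = 460 × *s*; per item = 460 × *s* / 46.

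| Assumed share | Recipients | Per item (46 items) |
|---|---|---|
| 10% | 46 | 1 |
| 20% | 92 | 2 |
| 30% | 138 | 3 |
| 50% | 230 | 5 |
| 80% | 368 | 8 |

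Section 2.6 cites 5 to 10 subjects per item. For the 19-item palliative subscale alone that is 19 × 5 = 95 to 19 × 10 = 190 patients, which needs a share of 95/460 = 21% to 190/460 = 41%. A subscale-level CFA in recipients may or may not be feasible. For all 46 items, the lower limit of 5 per item needs a share of 50%.

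**4. How far alpha could move.** Let *r* be the total-score variance in palliative patients divided by that in the enrolled sample, with error variance the same in both (assumption). Then

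alpha(palliative) = 1 − (1 − alpha(sample)) / *r*.

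Take alpha(sample) = 0.82, the English palliative-subscale value quoted in section 2.4, purely as an example:

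| *r* (assumed) | Calculation | alpha in palliative patients |
|---|---|---|
| 0.5 | 1 − 0.18/0.5 | 0.64 |
| 0.8 | 1 − 0.18/0.8 | 0.775 |
| 1.0 | 1 − 0.18/1.0 | 0.82 |
| 1.25 | 1 − 0.18/1.25 | 0.856 |
| 2.0 | 1 − 0.18/2.0 | 0.91 |

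The plan's limit of 0.7 for adequate reliability is crossed at *r* = 0.18/0.30 = 0.6. Neither the size of *r* nor whether it lies above or below 1 can be read from the documents.

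**The case against.** The enrolled group is not a different population. It is broader and can include many palliative-care recipients. The stated aim is also wide: the Methods paragraph of the abstract speaks of Iranian individuals with cancer and heart failure, the Background presents palliative care as applicable to chronic disease in general, and the concluding sentence is tentative. This stands as far as it goes, but being eligible for palliative care in principle does not make an enrolled patient a recipient.

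A mixed sample also serves a purpose. The known-groups comparison needs a spread of stages, and metastasis and heart failure class are already collected and checked with clinicians. A reader might infer that the study cannot say anything about advanced patients. The documents do not support that, because the stage data permit such an analysis. What the article states for them is only a comparison of means, which shows neither reliability nor factor structure in advanced illness.

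A reader might also infer that mixing early and advanced disease inflates alpha and omega. That is not supported either, since no variance is given for either group. If patients with early disease cluster at one end of the palliative items, item variance in the mixed sample shrinks, which can work against inflation.

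Finally, the clinical variables are listed as examples, so palliative status may be recorded after all, and the full protocol may hold more detail. That weakens any claim of omission. It does not remove the mismatch between the stated eligibility and the stated conclusion, which the limitations leave unmentioned.

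**Conclusion.** The point holds as a mismatch between the sample and the claim. The plan supports conclusions about inpatients and outpatients with cancer or heart failure at this centre. As written, it does not support a conclusion specific to patients receiving palliative care, because the article neither requires nor names that status and reports no reliability or structural result by it.

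The size of the consequence cannot be derived. The range of 0.64 to 0.91 around 0.82 is a two-directional illustration that rests on assumed variance ratios of 0.5 to 2.0, equal error variance, and an English coefficient standing in for the Persian result. It shows that the plan's 0.7 limit could be crossed, not that it will be. The study remains sound for the broader hospital population, so this is an inexpensive improvement that should be made, not a fatal flaw.

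**What to change.** 1. Record receipt of palliative care (yes/no) on the clinical form in section 2.4.
2. In section 2.6.1, prespecify reliability, floor and ceiling proportions and, where numbers allow, subscale-level CFA in patients receiving palliative care. Report the same separately in the advanced-stage subset (metastatic cancer, more severe heart failure classes). Do not treat advanced stage as equivalent to receiving palliative care.
3. Word the conclusion for inpatients and outpatients with cancer or heart failure. Claim use in palliative care only if the results in the palliative-care subset meet the thresholds already stated in section 2.6.1.
4. Add to section 3.1 that enrolment was not restricted to palliative-care recipients.

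The cost is one form field, subset estimates that are less precise than the overall ones, and a narrower conclusion. Recruitment, eligibility and sample size are unchanged. The field should be added before enrolment starts, since the status may be hard to recover later.
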